### Statistical Analysis

Analyses will be performed within the framework of intention-to-treat analysis. Sociodemographic and clinical characteristics will be summarized and compared between groups in the baseline. For the primary end point, the differences between proportions of adequate self-care maintenance in the 3-month follow-up will be assessed using the chi-square test (or the Fisher exact test if adequate) and performed to compare the first experimental arm (MI delivered only to patients) and control group and between the second experimental arm (MI delivered to the dyad) and control group.

In addition, beyond the comparison between proportions aimed to detect clinically meaningful differences between groups, the standardized 0-100 scores of self-care maintenance will be compared using a 1-way ANOVA with post hoc comparisons adjusting the significance according to Bonferroni. A stepwise logistic regression model based on a dichotomic outcome (adequate self-care vs inadequate self-care scores) will be used to encompass the effects of clinical and sociodemographic covariates in determining the association between the group and the proportion of adequate self-care. The first step of the stepwise approach will include the trial group as an independent variable to determine the odds ratios, highlighting the associations between each group and the dichotomic outcome. The second step will allow authors to include the covariates that show significant linear relationships with the outcome to adjust the associations described in the first step. This model will be evaluated using goodness-of-fit tests, such as the Hosmer-Lemeshow test. The same approach will be used by considering the standardized 0-100 scores of self-care maintenance as the dependent variable and, therefore, in the framework of multiple linear regression. While the logistic regression will provide an association between the adequacy of self-care maintenance and the arm by accounting covariates for adjusting the estimate, the multiple linear regression will highlight the amount of variance explained by belonging to each arm, accounting for the same covariates used in the logistic regression.

The analytical strategy for testing the secondary end points will be the same adopted for the primary end point. In addition, in the framework of time-to-event analysis, the cumulative probability of shifting from inadequate to adequate self-care (ie, the event will be defined as each shift from self-care maintenance scores under 70 to scores equal to or greater than 70) at 6, 9, and 12 months of follow-up after enrollment will be described using Kaplan-Meier curves and inferentially tested using log-rank tests.

The aims focused on testing the effect of the structured program based on MI interventions on secondary outcomes (eg, self-care monitoring, QoL, sleep disturbance) at 3, 6, 9, and 12 months from the enrollment and corroborating the superiority of the caregivers’ participation to the MI interventions over the MI interventions administrated only to individual patients in enhancing self-care behaviors are not used for determining specific end points. Therefore, the analytical plan for assessing those aims will be based on exploratory analyses based on comparing the secondary outcomes scores between the study arms.

In the case of missingness, analyzing the extent of the missingness and identifying underlying mechanisms and patterns will guide imputation methods. If missing at random criteria will be plausible, multiple imputations based on random effect models will be considered for missingness >5% of the outcome assessments at each time point of the trial. Inferential analyses will be based on an alpha of 5% and 2-tailed null hypotheses using Stata 17 (StataCorp).

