### Sample Size Calculation

For determining sample size, based on a recent literature review [33], it was hypothesized that both experimental arms would show an improvement in self-care maintenance, and the adequacy of self-care maintenance scores in the experimental arm was shown in approximately 50% (n=250) of patients. Current Italian data indicated that roughly 20% (n=238) of Italian adults with HF reported adequate scores of self-care maintenance (scores higher than 70 are considered adequate) [47,48]. For this reason, the sample size estimation was based on a 2-sample proportions test: the expected proportion in experimental arms was equal to 50% of adequate scores (proportion 1) versus 20% of the adequate score in the control group based on the current descriptive literature (proportion 2, delta=30%). Setting alpha at .05 and power at 0.90, the number per group to identify significant differences was equal to 52. Therefore, as the study has 3 arms, 156 participants are required to test the differences in proportions between groups. Given the likelihood of a 15% rate of dropouts as per previous studies [32], the total sample size was equal to 180 diads (n=60 per arm). A consecutive screening and enrollment will be performed.

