### End Points

The end points of this study are designed for the specific aim focused on testing the efficacy of a structured program, including scheduled MI interventions, in improving self-care maintenance. Precisely, the primary end point is the difference between self-care maintenance levels between the 2 groups in the 3-month follow-up. The secondary end points are the differences between self-care maintenance, self-care monitoring, and self-care management at 6, 9, and 12 months of follow-up after enrollment.

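### The primary end point is tested by two MI-versus-control comparisons with no multiplicity or success rule; if a win in either arm counts, the family-wise error is about 9.1%, not 5%

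*Protocol article*

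**What the plan says.** The End Points section of the protocol article states that "the primary end point is the difference between self-care maintenance levels between the 2 groups in the 3-month follow-up". The trial has three arms, and the section does not say which two groups are meant.

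The Statistical Analysis section gives the primary end point two tests of the proportion with adequate self-care maintenance at 3 months. A chi-square test, or Fisher's exact test, is used to "compare the first experimental arm (MI delivered only to patients) and control group and between the second experimental arm", where MI goes to the dyad, and the same control group. The section closes with a general rule: "Inferential analyses will be based on an alpha of 5% and 2-tailed null hypotheses". The Abstract repeats that level for comparisons between groups. The only multiplicity adjustment in the article is Bonferroni, for the post hoc comparisons of a further one-way ANOVA on the 0-100 scores.

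In the Sample Size Calculation section, "the sample size estimation was based on a 2-sample proportions test", with 50% adequate scores in the experimental arms and 20% in the control group. "Setting alpha at .05 and power at 0.90, the number per group to identify significant differences was equal to 52". That figure is multiplied by three arms to give 156, and raised to 180 dyads (60 per arm) for 15% dropout.

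**The concern.** Two tests share one control arm, each apparently at 5%, and one primary aim covers both: efficacy of the structured MI program. Both MI arms deliver that program and are planned at the same 50% rate. The article does not say whether one significant result is enough, whether both are needed, or whether one arm is tested first. A report could therefore claim the primary aim on the strength of either arm, and the chance of a false claim would then exceed the stated 5%. If the rule is left open until results are known, the choice between either and both can follow the data.

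The sample size has a related gap. It was derived for a single two-sample test, so its 90% says nothing direct about the probability of meeting the primary aim once two tests are involved.

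**Working it through.** **Inputs (Sample Size Calculation and Statistical Analysis sections).** Rates 0.50 (each MI arm) and 0.20 (control); two-sided alpha 0.05; power 0.90; three equal arms; 60 per arm randomised; 15% dropout, so 60 × 0.85 = 51 evaluable per arm; two primary comparisons against one control.

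**1. Reproduce the plan's figure.** Pooled-variance formula, no continuity correction, mean rate (0.50 + 0.20)/2 = 0.35:

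n = [z(1−α/2)·√(2 × 0.35 × 0.65) + z(0.90)·√(0.50 × 0.50 + 0.20 × 0.80)]² / 0.30²

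- α = 0.05: (1.322 + 0.821)² / 0.09 = 51.01, rounded up to 52. This matches the plan, so 52 is the size for one comparison at an unadjusted 5%.
- α = 0.025: (1.512 + 0.821)² / 0.09 = 60.45, rounded up to 61.

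Power for one comparison at 0.05 is 90.6% with 52 per arm and 90.0% with 51. The stated 90% is therefore correct for each of the two comparisons.

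**2. Family-wise error if either win counts.** With equal arms and a shared control, the two test statistics have correlation 0.5. Under no effect in either arm:

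1 − P(|Z1| < 1.96 and |Z2| < 1.96) = 0.0907

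Simulation of the two chi-square tests with 20% in every arm gives 9.1% at 52 per arm and 9.0% at 60. Independent tests would give 1 − 0.95² = 9.75%; the shared control lowers this a little.

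**3. If both must win.** The rejection rate for both tests under the same null is about 1%, so there is no inflation. Power for both at an unadjusted 5%, with true rates 50%/50%/20%, is 83% at 51 per arm and 85% at 52.

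**4. Power by procedure (simulation, 50%/50%/20%).**

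| Procedure | Evaluable per arm | Each comparison | At least one | Both |
|---|---|---|---|---|
| Unadjusted 5% each | 51 | 90% | 97% | 83% |
| Unadjusted 5% each | 52 | 91% | 97% | 85% |
| Holm, family-wise 5% | 51 | 88% | 94% | 83% |
| Holm, family-wise 5% | 60 | 93% | 97% | 90% |
| Bonferroni, 2.5% each | 51 | 84% | 94% | 75% |

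Under the null, Holm brings the family-wise error to about 4.6% at 51 per arm.

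**The case against.** The strongest reply is that the 9.1% depends on a success rule the article never states. The sample size text expects improvement in both experimental arms, and if both tests must succeed nothing is inflated. Patient-only MI and dyad MI could also be treated as separate questions, each with its own 5%, which some statisticians accept. The alpha sentence does not say whether 5% is per test or per family, and the article condenses a fuller protocol.

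Part of this stands: the either-wins rule is an inference and must be presented as one. It is a natural inference, because the primary aim is a single claim about the program and no separate claim is stated for each arm. The unseen full protocol does not remove the point either. The article carries 0.05 unsplit into its sample size, attaches no adjustment to the two primary tests, and names Bonferroni only for the additional ANOVA.

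A reader might go further and infer that the 90% power belongs to only one of the two comparisons, or that the trial falls to 84% once corrected. Neither follows. Each comparison has about 90% at the unadjusted level. The 84% is for a fixed 2.5% per test at 51 evaluable; Holm gives about 88%, and the chance of at least one success stays near 94%. Those are also the figures at full planned dropout: with all 60 per arm evaluable, power at a fixed 2.5% is 89.8%. That is an upper bound, since imputation does not restore full information.

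**Conclusion.** The point holds as a gap in the primary decision rule. The End Points and Statistical Analysis sections do not agree on what the primary comparison is, and no rule links the two tests to the primary aim. If either win counts, the false-positive risk for that aim is about 9.1% against a stated 5%. If both must win, the error is controlled but joint power is about 83% to 85%, not 90%. On neither reading do the stated alpha and power both describe the pair of tests.

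The 9.1% assumes equal arms, no effect in either MI arm and the either-wins reading. The power figures assume the planned 50%/50%/20% and 51 to 60 evaluable per arm. The effect on power is moderate; type I error is the main issue.

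**What to change.** Before between-arm results are seen, rewrite the primary end point and its analysis as two named contrasts in the proportion adequate at 3 months: patient-only MI versus control, and dyad MI versus control. Test them by Holm at a two-sided family-wise 5%: the smaller p-value against 0.025 and, if that is significant, the larger against 0.05. State which conclusion each pattern of results supports. A prespecified fixed order would also control the error and would leave the 52-per-group calculation intact for the first test.

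Restate power for the chosen procedure. Under Holm at 50%/50%/20% it is about 88% per comparison, 94% for at least one and 83% for both at 51 evaluable per arm, rising to about 93%, 97% and 90% if all 60 are evaluable. Keep dyad versus patient-only MI outside this family as exploratory, as the Statistical Analysis section already does.

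The cost is wording, plus about 2 points of power per comparison (90% to 88% at 51 per arm), which puts it slightly below the stated 90% at the planned dropout. No patients are added; follow-up ended in May 2021, so the sample size could not be changed in any case.

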## Introduction

Heart failure (HF) is defined as “a clinical syndrome with symptoms and or signs caused by a structural and/or functional cardiac abnormality and corroborated by elevated natriuretic peptide levels and or objective evidence of pulmonary or systemic congestion” [1]. HF is characterized by an increasing prevalence and burden, representing a public health problem and a major cause of morbidity and mortality [1,2]. Globally, the overall estimated incidence of HF disease is 1-4 cases per 1000 person-years, with a prevalence of 10-30 cases per 1000 persons [3]. The incidence of the disease in Europe is about 5 per 1000 person-years, with a prevalence of 1%-2% in adults [4]. The prevalence of HF increases significantly with age: 6.6% of men with HF are aged 60 to 79 years, and 10.6% are aged 80 years and older [5].

Due to the impact of the disease, some authors have defined HF to be the “global outbreak” of the 21st century about 25 years ago [6,7]. An estimated 64.3 million people worldwide are affected by HF [7]; the growing and aging of the population, the high survival rate after an acute coronary event, and the effectiveness of secondary prevention and drug treatment result in a constant increase in the number of patients living with HF [4,7-9]. HF is most frequently diagnosed in patients who are hospitalized and 65 years and older [10]. People surviving at 1 and 5 years of follow-up have increased by about 20% compared to 1950-1970s [11]; however, 5-year mortality is still high, resulting in 24.4% for people aged 60 years and 54.4% for people aged 80 years [5].

Outcomes related to HF have improved in recent years [4]. Thus far, hospitalization and rehospitalization still impact the health care system; treating patients with HF costs US $30 billion every year, and this figure is destined to grow further, reaching US $70 billion by 2030 in the United States [5]. Once HF is first diagnosed, patients are readmitted to the hospital about once a year; this trend contributes to increasing health care resource consumption and worsens patients’ quality of life (QoL) [7,12]. Moreover, HF is associated with considerable morbidity and mortality [13]. A 60- to 90-day mortality from diagnosis is about 10% in patients with HF; 1-year mortality is about 36% [14].

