### Sample and Setting

Outpatients referred to the heart failure clinic and inpatients at discharge after hospitalization for HF will be enrolled in the study. The single center where the study will be implemented is the IRCCS Policlinico San Donato, northern Italy. The recruitment strategy will be based on enrolling patients continuously until the predetermined sample size is achieved.

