### Inclusion and Exclusion Criteria

The following inclusion criteria will be used for patients: being 18 years and older, diagnosis of HF with New York Heart Association (NYHA) Class II-IV, no acute coronary events within 3 months, consent to participate in the study, score ≤ 2 to at least 2 items of the Self-Care of Heart Failure Index 6.2 (SCHFI 6.2) at baseline [34], scores on Six Item Screener >4 [35], living at home, understanding of spoken and written Italian. The exclusion criteria for patients will be severe cognitive impairment (score 0-4 on the Six-item Screener) [35], acute coronary events that occurred within 3 months, living in nursing homes or residential settings, and caregivers unwilling to participate in the study.

The following inclusion criteria will be used for caregivers: being 18 years or older, being the primary informal caregiver identified by the patient, consent to participate in the study, and understanding of spoken and written Italian. Their unavailability will give the exclusion criterion for caregivers to participate in the study.

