Although MI is effectively largely used either alone or combined with other treatments and is administered in different settings and ways (ie, patients’ homes; over the telephone; and in hospitals, clinics, or nursing homes), face-to-face interventions seem to be more effective [49]. There is rationale to believe that a more intensive intervention program would even ameliorate and better support patients’ self-care behaviors. Moreover, involving caregivers in this intensive intervention program would make them feel more participatory and aware of the patient’s care process, recognizing their pivotal role in disease management and enhancing their knowledge about HF disease. Besides, dyads with higher shared HF knowledge are more efficient in promoting self-care adherence behaviors [29]. Moreover, both patients and caregivers may perceive proximity with health care professionals, resulting in a better ability to follow the received health professionals’ directions [50]. Self-care is built up on attitudes, behaviors, knowledge, and self-efficacy, and the literature suggests that HF self-care management is more challenging than self-care maintenance and is enhanced by the presence of a caregiver who needs to be properly trained and involved [50,51].

This study protocol presents some limitations that need to be pointed out. First, the monocentric design could affect the generalizability of the results, and the nature of the intervention does not permit a double-blind study design. Moreover, the rather short follow-up (1 year) does not give correct estimates of the lifetime effects of the intervention. Lastly, study participants might be healthier than the average person with HF, as they are usually health conscious with a better lifestyle.

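### Kaplan-Meier curves with no rule for deaths will, in standard use, overstate the 12-month probability that an enrolled patient shifts to adequate self-care

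*Protocol article*

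**What the plan says.** In the protocol article, the Statistical Analysis section adds a time-to-event analysis to the secondary end points. Its target is "the cumulative probability of shifting from inadequate to adequate self-care", where the event is a crossing of the score of 70 on self-care maintenance. The probability "at 6, 9, and 12 months of follow-up after enrollment will be described using Kaplan-Meier curves and inferentially tested using log-rank tests". Death is not part of the event. The section names no competing event and gives no rule for deaths. The only nearby provision is multiple imputation of missing assessments where missing at random is plausible.

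Three other places bear on how many deaths to expect:
- Sample and Setting: "Outpatients referred to the heart failure clinic and inpatients at discharge after hospitalization for HF will be enrolled in the study".
- Inclusion and Exclusion Criteria: "diagnosis of HF with New York Heart Association (NYHA) Class II-IV".
- Introduction: "A 60- to 90-day mortality from diagnosis is about 10% in patients with HF; 1-year mortality is about 36"%.

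Against this, the Discussion notes that "study participants might be healthier than the average person with HF".

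**The concern.** The target and the estimator do not match. Death before a shift rules the shift out, so it is a competing event. The Kaplan-Meier estimator has a single event type. In standard use a death leaves the risk set as censored, and the estimator in effect lets that patient go on to shift at the survivors' rate. One minus Kaplan-Meier (1-KM) is then the probability of shifting if nobody died, not the proportion of enrolled patients who reach adequate self-care.

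If the curves are read as that proportion, they are too high wherever deaths precede shifts. With similar mortality across arms, the excess is larger where shifting is more common, so the absolute benefit of MI looks somewhat larger too. Imputing missing scores would not cure this, because scores imputed after death refer to the same population without deaths.

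**Working it through.** **Inputs from the protocol article.** 50% adequate scores in the experimental arms, 20% in control, and 60 dyads per arm (Sample Size Calculation); questionnaires at 3, 6, 9 and 12 months (Intervention and Participant Timeline); background one-year mortality of 36% (Introduction).

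**The plan's own figure.** The plan gives no figure for these curves. The calculation that supplies the 50% and 20% does reproduce: with pooled variance and two-sided alpha 0.05, n = [1.96 × √(2 × 0.35 × 0.65) + 1.2816 × √(0.25 + 0.16)]² / 0.30² = 51.01, rounded up to 52 per group, as stated.

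**Assumptions.** The 50% and 20% are borrowed as death-free 12-month shift probabilities F. Hazards of shift and death are constant, independent, and (for death) equal across arms. One-year mortality m is set at 5%, 10%, 15% and 36%.

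**Formulas.** Death-free probability by month t: F(t) = 1 − (1 − F)^(t/12). Survival: S(t) = (1 − m)^(t/12). With deaths censored, 1-KM estimates F(12). The cumulative incidence (CIF) is the sum over visits of the increment in F(t) times S(t).

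**Worked case, F = 0.50, m = 0.36.** Increments are 0.1591, 0.1338, 0.1125 and 0.0946; survival is 0.8944, 0.8000, 0.7155 and 0.6400. CIF = 0.1423 + 0.1070 + 0.0805 + 0.0605 = 0.390, against 0.500 by 1-KM.

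| One-year mortality | MI arm CIF (1-KM 50%) | Excess, points | Control CIF (1-KM 20%) | Excess, points | Arm difference by CIF (1-KM 30) |
|---|---|---|---|---|---|
| 5% | 48.6% | 1.4 | 19.4% | 0.6 | 29.2 |
| 10% | 47.1% | 2.9 | 18.8% | 1.2 | 28.3 |
| 15% | 45.6% | 4.4 | 18.1% | 1.9 | 27.5 |
| 36% | 39.0% | 11.0 | 15.4% | 4.6 | 23.7 |

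Arm differences are taken before rounding. Simulation of 400,000 patients per setting agrees: at 36% mortality, 1-KM gives 0.499 against a CIF of 0.389, and 0.200 against 0.154.

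**Sensitivity to timing.** At 15% mortality, if 60%, 80%, 90% and 100% of shifts have occurred by months 3, 6, 9 and 12, the excess is 3.3 points (MI) and 1.3 (control). With equal shift hazards at months 6, 9 and 12 only, it is 5.4 and 2.2. In continuous time, CIF = λs/(λs + λd) × [1 − exp(−(λs + λd))], with λs = −ln(1 − F) and λd = −ln(1 − m) per year. The excess is then 3.4 and 1.5 points at 15% mortality, and 8.6 and 3.7 at 36%.

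**Which mortality is plausible.** The Introduction also gives 5-year mortality of 24.4% at age 60 and 54.4% at age 80. Under a constant hazard the one-year equivalents are 1 − 0.756^(1/5) = 5.4% and 1 − 0.456^(1/5) = 14.5%. Hence the main range of 5% to 15%.

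**Scale against sampling error.** With 60 per arm, the standard error is √(0.5 × 0.5/60) = 6.5 points at 50%, √(0.2 × 0.8/60) = 5.2 points at 20%, and √(6.5² + 5.2²) = 8.3 points for the difference.

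**The case against.** The strongest reply is that the article names Kaplan-Meier but states no censoring rule, so an error has not been shown. A reader might infer that Kaplan-Meier can only censor deaths and must be too high in every arm. The document does not support that. If patients who die are kept in the risk set to month 12 and there is no other censoring, 1-KM equals the cumulative incidence; the simulation confirms it. An excess in a given arm also needs at least one death before a shift there, with later shifts among survivors. What remains is that nothing in the plan departs from standard use, that dropout is expected ("Given the likelihood of a 15% rate of dropouts as per previous studies"), and that deaths are likely: even at 5% mortality, the chance of none among 60 patients is 0.95^60, about 5%.

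A reader might also take 11 points as the expected error. The 36% is a background figure, not a trial assumption, and the Discussion says participants may be healthier. The planned 15% covers all dropout, not deaths alone. In the 5% to 15% range the excess is below one standard error in each arm. The 50% and 20% were set for the 3-month comparison, so they only illustrate scale here.

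Finally, the curves come on top of the comparisons of proportions and scores at 6, 9 and 12 months. The log-rank test with deaths censored remains a valid test of the cause-specific hazard of shifting. Both points stand and limit the weight of the finding, but they do not make the plotted probability right.

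**Conclusion.** The point holds in a limited form. The plan fixes a cumulative probability as its target and a single-event estimator to describe it, with no rule for deaths in a population where deaths within 12 months are to be expected. In standard use the curve overstates the probability that an enrolled patient shifts. Under the assumptions above, the excess is about 1.4 to 4.4 points in an MI arm and 0.6 to 1.9 in control at 5% to 15% one-year mortality, with 11 and 4.6 points as the upper extreme at 36%.

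The upward direction within an arm is firm once deaths before a shift are censored; the size is uncertain. The inflation of the arm difference, about 0.8 to 2.5 points in the main range (30 less 29.2 and 27.5), also rests on similar mortality across arms. It could reverse if control mortality were much higher: with 5% in the MI arm and 36% in control, the CIF difference would be 48.6 − 15.4 = 33.2 points, not 30.

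It would be wrong to conclude that the log-rank test is invalid or that the main result is at risk. This is a supplementary secondary analysis; the primary 3-month test and the sample size are unaffected.

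**What to change.** In the Statistical Analysis section, replace the Kaplan-Meier curves with Aalen-Johansen cumulative incidence curves for the first shift to adequate self-care maintenance. Treat death before the shift as a competing event, and censor only withdrawal and loss to follow-up. Compare the curves with Gray's test, or keep the log-rank test and label it a test of the cause-specific hazard of shifting. Report the number of deaths by arm beside the curves.

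The cost is one sentence in the plan and a competing-risks routine; no further patients or visits are needed. The date of death, or at least the visit interval in which it fell, must be available. The article does not list it among the data collected, so this should be confirmed before analysis. The reported probabilities will be slightly less favourable than the Kaplan-Meier ones.

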### Intervention and Participant Timeline

All patients meeting the inclusion criteria and not any exclusion criteria will be randomized by the researchers responsible for the study after having signed a consent form. Patients will be informed about the single allocation and will not be aware of the randomization list and allocation sequence. The intervention will be administered by nurses trained in HF self-care and MI.

The study flowchart is shown in Figure 1. In the first interventional arm, the MI intervention will be administered to patients only, and caregivers will receive standard education. MI is used to reinforce areas of inadequate self-care (eg, low physical activity or not having a low-salt diet) and to agree with the patients on the steps to be adopted to modify their behavior. MI focuses on a tailored patient approach to improve patients’ adherence to self-care behaviors. The intervention will last approximately 30 minutes. Thereafter, the nurse who performed the MI will contact the patients over the phone 3 times every 2 weeks from the first MI during the first 2 months after MI to strengthen the intervention. Then, the intervention will be used again after 3, 6, 9, and 12 months from enrollment. After each MI session, both patients and caregivers will be asked to complete the follow-up questionnaires post enrollment as described in the “Instrument” section. In the second interventional arm, MI intervention will be administered both to patients and caregivers. The intervention will be administered to the dyad in 1 session, and patients and their caregivers will receive the reinforcing educational treatment calibrated on the specific lacking areas of patients’ self-care behaviors. After each MI session, both patients and caregivers will be asked to complete the follow-up questionnaires post intervention. In the control group, the dyads will receive only traditional educational treatment and complete the questionnaires after 3, 6, 9, and 12 months of follow-up post intervention. Enrolled dyads will be monitored by the research team responsible for recruitment and follow-up.

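### The time-to-event analysis counts every shift to adequate self-care, but Kaplan-Meier curves and log-rank tests use one event per patient

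*Protocol article*

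**What the plan says.** All references are to the protocol article.

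- **Target, event and method (Statistical Analysis).** Beyond the tests of the secondary end points, the plan adds an analysis of "the cumulative probability of shifting from inadequate to adequate self-care". In it, "the event will be defined as each shift from self-care maintenance scores under 70 to scores equal to or greater than 70". The probability "at 6, 9, and 12 months of follow-up after enrollment will be described using Kaplan-Meier curves and inferentially tested using log-rank tests". Tests are two-sided at 5%.
- **Visits (Intervention and Participant Timeline; End Points).** Control dyads "complete the questionnaires after 3, 6, 9, and 12 months of follow-up post intervention", and maintenance at 3 months is the primary outcome: "the primary end point is the difference between self-care maintenance levels between the 2 groups in the 3-month follow-up". The secondary end points concern "self-care maintenance, self-care monitoring, and self-care management at 6, 9, and 12 months of follow-up after enrollment".
- **Entry (Inclusion and Exclusion Criteria).** Patients need a "score ≤ 2 to at least 2 items of the Self-Care of Heart Failure Index 6.2 (SCHFI 6.2) at baseline". Instruments and Outcomes says that this index has three dimensions, each scored separately from 0 to 100.

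The article does not say how a relapse below 70 is handled, who is at risk, or what time is assigned to an event.

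**The concern.** The event and the method do not match. If every upward crossing of 70 is an event, a patient who improves, relapses and improves again supplies two. A Kaplan-Meier curve is a cumulative probability only if each patient contributes at most one event. The ordinary log-rank variance likewise has no term for repeated events in the same patient.

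Relapse is plausible on the article's own account. The Introduction reports that, in an earlier trial of a single session, effects on confidence and on proxy measures of behavior faded after 3 months. The Discussion makes persistence over one year an aim. Followed literally, the analysis could give a curve that overstates the probability and a log-rank p-value that is too small.

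Two gaps in the same sentence add to this: whether the 3-month visit counts, and whether patients already adequate at baseline are in the analysis.

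**Working it through.** **The plan's own figure.** No event count, hazard ratio or power is given for the log-rank analysis. The sample size of 52 per group belongs to the primary comparison. It reproduces with the pooled two-proportion formula: [1.96·√(2·0.35·0.65) + 1.2816·√(0.25 + 0.16)]² / 0.30² = 51.0, rounded up to 52. It does not bear on this point.

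**Inputs.** From the article: visits at 3, 6, 9 and 12 months, 60 patients per arm, 15% dropout, two-sided 5%. Assumed, because the article gives none: the chance *p* per visit that an inadequate patient becomes adequate, and the chance *q* per visit that an adequate patient relapses. All patients start below 70.

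**1. Can a patient shift more than once?** Two shifts need up, down, up, which fits in four visits with one visit to spare. Three shifts would need five visits. So P(two shifts) = p²q(4 − 2p − q).

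| p | q = 0.1 | q = 0.3 | q = 0.5 |
|---|---|---|---|
| 0.2 | 0.014 | 0.040 | 0.062 |
| 0.5 | 0.073 | 0.203 | 0.313 |

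The chance of at least one shift by month 12 is 1 − (1 − p)⁴, which is 0.938 at p = 0.5. Mean shifts per patient are then 0.938 + 0.073 = 1.01 (q = 0.1) up to 0.938 + 0.313 = 1.25 (q = 0.5). A mean above 1 is not a probability.

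**2. Effect on the curve.** Suppose patients re-enter the risk set whenever they are below 70. If *p* is the same for everyone, the every-shift curve is still 1 − (1 − p)⁴ at 12 months and there is no bias. If *p* varies, the patients who re-enter are those who shift easily, and the curve runs high from month 9. With *p* following a beta distribution with parameters summing to 2, the true 12-month value is:

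- mean 0.2: 1 − (1.6/2)(2.6/3)(3.6/4)(4.6/5) = 0.43
- mean 0.5: 1 − 1/5 = 0.80

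The simulated every-shift curve at 12 months, for q = 0.3 and 0.5, reads 0.47 and 0.49 (mean 0.2), and 0.87 and 0.89 (mean 0.5).

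**3. Effect on the log-rank test.** Two arms of 60 with no true difference, 15% dropout, 10,000 runs:

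| Mean p (beta sum), q | First shift only | Every shift |
|---|---|---|
| 0.2 (2), 0.3 | 0.050 | 0.080 |
| 0.2 (2), 0.5 | 0.048 | 0.090 |
| 0.5 (2), 0.5 | 0.054 | 0.110 |
| 0.3 (1), 0.5 | 0.052 | 0.118 |

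**4. The 3-month visit.** If 6, 9 and 12 months are reading points on a curve from enrollment, nothing is lost. If 3-month data are left out, patients adequate at 3 but not at 6 months are missed. The 6-month value becomes p(1 − q) + (1 − p)p instead of 1 − (1 − p)². At p = 0.2 that is 0.26 to 0.34 instead of 0.36; at p = 0.5 it is 0.50 to 0.70 instead of 0.75 (q from 0.5 to 0.1). At 12 months the loss is at most about 0.06.

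**5. Risk set.** Two low items on the confidence or management dimension meet the entry criterion. A patient can therefore enter with adequate maintenance and have no first shift from inadequate to adequate to observe.

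**The case against.** The strongest reply is that the word *each* is loose. Naming Kaplan-Meier, log-rank and a cumulative probability implies the usual first-event analysis, and the harm arises only if an analyst counts repeats. It also needs variation between patients, as step 2 shows. That is fair, and a first-event reading is possible. But the sentence states an event rule, and taken as written the rule is the wrong one for the method.

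Three stronger readings are tempting but not supported:

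- **That visit-based timing invalidates the curves.** The article never says that times are treated as exact. On a common schedule with complete visits, the grid curve equals the true curve at the visits: an assumed exponential onset with mean 12 months gives 0.22, 0.39, 0.53 and 0.63 both ways. The first-shift log-rank test on tied visit times keeps its level (step 3). Interval censoring matters only between visits or when visits are missed or irregular.
- **That the 3-month data are excluded.** The months listed are those of the secondary end points and may simply be reporting times.
- **That a fifth of patients are not at risk and dilute the curve.** The 20% in Sample Size Calculation describes Italian adults with heart failure and serves as the expected control proportion. This sample is selected for low items, and nothing says that already-adequate patients stay in the risk set. Starting from scores under 70 even suggests the opposite.

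The analysis is also an addition, since the secondary end points have their own tests.

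**Conclusion.** The point holds for the event definition: a recurrent event does not fit a Kaplan-Meier probability or an ordinary log-rank test. The sizes in steps 2 and 3 (a 12-month curve too high by about 0.04 to 0.09; type I error of about 0.08 to 0.12) rest on assumed rates, on variation between patients, and on repeats actually being counted. They show what could happen under the stated rule and do not predict this trial's result. The 3-month visit and the baseline risk set are matters to clarify, not demonstrated errors. A reader should not infer that the primary analysis is at risk: the primary end point and the sample size do not depend on this analysis.

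**What to change.** Define the event as the first visit with adequate maintenance among patients whose maintenance is inadequate at baseline. State that the 3-, 6-, 9- and 12-month visits all count, and that 6, 9 and 12 months are reading points if that is what is meant. Kaplan-Meier and log-rank on the visit grid can stay; a discrete-time model is optional.

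The same edit should settle a score of exactly 70. The event rule treats it as adequate, whereas Instruments and Outcomes and Sample Size Calculation require more than 70.

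The cost is a change of wording and code. Data collection is complete, and the article describes the analysis as still planned. The downside is a somewhat smaller risk set, because patients already adequate at baseline leave this analysis.
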